#### **7.6 Follow-up of subjects withdrawn from treatment**

After administration of the active vaccine, (serious) adverse events that occur in subjects that are withdrawn from the study procedure and preferably antibody titers, will still be recorded if possible.

#### **7.7 . Premature termination of the study**

Termination based on safety aspects: A multidisciplinary team with study investigators ([co]PI's and dedicated research physicians) together with the sponsor will discuss safety aspects during the study procedures.

The CTCAE stopping rules for first in human studies will be leading to grade a possible SAE and how to proceed if an SAE occurs.

The termination rules are as follows: When an SAE and/or AE  $\geq$  grade 3 NCI CTCAE (attributable to AKS-452X) occurs after the s.c. injection: terminate the study for all cohorts (e.g. if an SAE occurs in cohort 1, 2, 3, or 4, terminate the entire study).

Termination based on other aspects: The study will be suspended based on urgent medical or ethical considerations as decided by the principal investigators (additional to section 8.7). In case of termination of the study, the sponsor, the institution, regulatory authorities (CCMO will be informed. Moreover, sponsor's medical monitor (or designee) may stop or suspend the trial due to safety concerns from the sponsor. Furthermore, sponsor may stop the trial due to other concerns.

Mandatory: A cohort must demonstrate a minimum of 80% seroconversion (in case a subject dropouts before day 28, he/she will be replaced with another subject. A cohort must include a

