#### 4.4 Sample size calculation

The study consists of a Phase II clinical study. The following stopping-rule will be applied on a cohort-by-cohort basis: for a particular cohort, any SAE or AE  $\geq 3$  (according to NCI Common Terminology Criteria for Adverse Events [CTCAE]) attributable to AKS-452X.

On the basis of the phase I/II safety assessment data conducted and a minimum project enhanced immune response rate of 80% for each cohort.

Enhanced immune response rate is defined as:

- i) Seroconversion based on a true positive based on the SP/RBD IgG ELISA assay positive/negative cutoff criteria using the quantitative cut-off value defined by the assay kit batch expressed in  $\mu\text{g/mL}$ . The positive/negative cutoff value was established as 2.42  $\mu\text{g/mL}$  from the validation analysis for the current lot of assay kits, but it should be noted that for each new lot of assay kits, Akston QC performs a re-validation of the cutoff value in order to maintain clinical agreement from lot-to-lot, and/or
- ii) Two times (2x) the baseline SP/RBD IgG at day 28 after boosting, as compared to the titer just before vaccination (day 0).

Based on the observed seroconversion rates in phase I/II and the statistical assessment for the phase II ACT-BOOSTER, a total study group of 150 subjects per cohort of registered vaccine (i.e. Pfizer [Comirnaty], Moderna [Spikevax], Janssen [Ad26.COV2.S], AstraZeneca [Vaxzevria]), totalling 600 subjects is regarded statistically significant to confirm the hypothesis. The statistical assessment providing the above stated numbers is based on the following argumentation (see Table 2 and Figure 9).

| Fixed Scenario Elements |                      |
|-------------------------|----------------------|
| Method                  | Normal approximation |
| Number of Sides         | U                    |
| Null Proportion         | 0.7                  |
| Nominal Power           | 0.8                  |
| Variance Estimate       | Null Variance        |
| Alpha                   | 0.05                 |

| Computed N Total |            |              |         |
|------------------|------------|--------------|---------|
| Index            | Proportion | Actual Power | N Total |
| 1                | 0.80       | 0.800        | 119     |
| 2                | 0.82       | 0.802        | 81      |
| 3                | 0.84       | 0.803        | 58      |
| 4                | 0.86       | 0.803        | 43      |

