| 5                | 0.88       | 0.806        | 33      |
| 6                | 0.90       | 0.812        | 26      |
| 7                | 0.92       | 0.802        | 20      |
| 8                | 0.94       | 0.807        | 16      |

**Table 2:** The POWER procedure Z test for binomial proportion

[figure not shown]

**Figure 9.** The POWER procedure Z test for binomial proportion

- If we consider a realistic minimum 80% conversion rate outcome in the phase II ACT-BOOSTER study, each treatment cohort will consist of 119 subjects. Considering a drop-out rate of 20%, this relates to 150 subjects per cohort (totaling 600 subjects). The minimum 80% conversion rate is considered realistic since the one single-dose injection cohort of 90 µg and the two-dose injection of 45 µg each demonstrated a 100% conversion rate in phase I/II.

Based on the above assessment of the statistical analysis, a total of 150 subjects per registered vaccine cohort will be included for the Phase II ACT-BOOSTER study, as this relates to a realistic outcome estimate based on the phase II ACT-study seroconversion rates for a single-dose injection group of 90 µg (26 subjects) and two-dose injection group of 45 µg (26 subjects), totaling 52 participants.

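### The 80% power in Section 4.4 belongs to a test against 70%, not to the mandatory 80% requirement in Section 7.7, which a cohort with a true rate of 80% meets only about half the time

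*Protocol*

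**What the plan says.** Section 4.4 bases the cohort size on Table 2, captioned "The POWER procedure Z test for binomial proportion". The inputs are an upper one-sided test ("Number of Sides | U") at alpha 0.05, with "Null Proportion | 0.7" and "Nominal Power | 0.8". The row used is "0.80 | 0.800 | 119": true proportion, power, N. The text then says "If we consider a realistic minimum 80% conversion rate outcome in the phase II ACT-BOOSTER study, each treatment cohort will consist of 119 subjects", and "Considering a drop-out rate of 20%, this relates to 150 subjects per cohort".

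Section 7.7, after the safety termination rules and under the label Mandatory, says "A cohort must demonstrate a minimum of 80% seroconversion". It sets a minimum of 119 subjects per cohort for the final analysis and defines the response by two limbs. It mentions neither the 70% null nor a test or confidence bound. Section 4.4, for its part, says nothing about the chance that a cohort reaches an 80% requirement.

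The two sections also time the response differently. The doubling limb is assessed at day 28 in Section 4.4 and at day 56 in Section 7.7. The primary endpoint in Section 7.1.1 is at day 28.

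**The concern.** The figure of 80% does two jobs. In Section 4.4 it is the assumed true rate at which a test against 70% has 80% power. In Section 7.7 it is the level a cohort has to demonstrate. When a hurdle equals the true rate, the estimate falls on either side of it about equally often, whatever the sample size. The stated power therefore describes a criterion other than the only explicit immunogenicity requirement in the protocol.

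What is at stake is how a cohort in the high seventies would be read. It can clear the test that justified the sample size and still fall short of the mandatory level. The study is open-label, so if this is left open the choice between the two could be made after the results are known.

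**Working it through.** **Inputs.** From Section 4.4, Table 2: p0 = 0.70, p1 = 0.80, one-sided alpha 0.05, power 0.80; drop-out 20%. From Section 7.7: at least 80% per cohort, at least 119 analysed.

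**1. The plan's own figure.** n = [z(0.95)·√(p0(1−p0)) + z(0.80)·√(p1(1−p1))]² / (p1−p0)²
= [1.645·√0.21 + 0.8416·√0.16]² / 0.10²
= (0.7538 + 0.3366)² / 0.01 = 118.9, so 119 with power 0.800.
The same formula reproduces all eight rows of Table 2. With drop-out, 119/0.80 = 148.75, so 149, which the protocol rounds to 150.

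**2. What the sized test requires.** The critical proportion at n=119 is 0.70 + 1.645·√(0.21/119) = 0.7691. Multiplied by 119 this is 91.5, so 92 responders (77.3%). The exact binomial alpha is 0.048 and the exact power at a true 80% is 0.804.

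**3. What the 80% requirement needs, read as an observed rate.** At n=119, 0.80·119 = 95.2, so 96 responders. Pass probabilities are exact binomial tails at a true rate of 80%. Because 119 is a minimum, n=120 (150 less 20%) and n=150 (no drop-out) are shown too.

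| n analysed | Needed for observed ≥80% | P(met), true 80% | Needed for test against 70% | Power, true 80% |
|---|---|---|---|---|
| 119 | 96 | 0.482 | 92 | 0.804 |
| 120 | 96 | 0.554 | 93 | 0.790 |
| 150 | 120 | 0.549 | 115 | 0.868 |

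The lower value at n=119 partly reflects rounding 95.2 up to 96. Going from 120 to 150 subjects raises the power of the sized test but does not help the 80% requirement.

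**4. Sensitivity to the true rate.** Probability of missing the 80% requirement:

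| True rate | n=119 | n=150 |
|---|---|---|
| 80% | 0.518 | 0.451 |
| 82% | 0.303 | 0.225 |
| 84% | 0.133 | 0.077 |
| 85% | 0.077 | 0.038 |
| 90% | 0.0007 | 0.0001 |

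Solving P(met) = 0.80 gives a true rate of 83.1% at n=119 and 82.3% at n=150.

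**5. A stricter reading.** If demonstrating 80% meant rejecting a rate of 80% or less at one-sided 0.05, a cohort of 119 would need 103 responders (86.6%). The chance of that at a true 80% is 0.042. The observed-rate reading is therefore the one most favourable to the plan.

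**The case against.** The strongest reply is that 80% is presented as a floor, not as the expected rate. Section 4.4 supports it with 100% conversion in the earlier phase I/II study, and at a true rate of 85% or more the 80% requirement is rarely missed. That stands, and it limits the practical size of the problem. It does not remove the mismatch, because N was set at 80%. Nor does the 100% carry over directly. It came from primary vaccination with the adjuvanted product, and Section 3 (Figure 8) reports day 0 samples below the quantification limit. Here subjects are already vaccinated, and under Section 7.1.1 those at or above the cutoff at baseline must double their titre.

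A second reply is that a design may deliberately ask both for significance against 70% and for an estimate at target, accepting roughly even odds at the target. That is legitimate, but the protocol does not say it intends this, and the 80% power would still need restating.

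Four stronger readings are tempting, and the documents do not support them:
- **A cohort below 80% fails or is terminated.** Section 7.7 sits under premature termination but states no consequence for missing 80%.
- **The study almost certainly fails because all four cohorts must pass.** The requirement is worded per cohort, and Section 7.1.1 reports each cohort separately. No all-four rule exists.
- **A cohort with 92 to 95 responders of 119 is positive under 4.4 and negative under 7.7.** This holds only if both sections count the same responders, and their doubling limbs refer to different days.
- **The sample size is miscalculated.** Table 2 is correct for the hypothesis it states.

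The absence of the 70% null from Section 9.3 is not counted against the plan, since the primary test may be specified in an analysis plan that is not shown.

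**Conclusion.** The point holds as an inconsistency between the hypothesis that was powered and the criterion that is mandatory. At the sizing value of 80%, a cohort meets the Section 7.7 requirement with probability 0.48 to 0.55, depending on the number analysed, against a stated power of 0.80. The risk of missing it is 45% to 52%, not 20%.

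These figures rest on three assumptions: Section 7.7 refers to an observed rate, the true rate is exactly 80%, and responses are independent between subjects. The first is the lenient choice; a confidence-bound reading makes the gap larger. The second is the plan's own sizing value; a true rate a few points higher closes most of the gap.

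**What to change.** Reconcile Sections 4.4 and 7.7 by one of two routes.

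1. **Use the criterion that was sized.** Replace the 80% requirement in 7.7 with a one-sided 95% lower confidence bound above 70%, evaluated at the number actually analysed: for example at least 92 of 119, or at least 115 of 150. Defining it by the bound avoids fixing a count that is right only at the minimum n. The power statement in 4.4 then stands.
2. **Keep the 80% requirement.** State in 4.4 that a cohort with a true rate of 80% meets it about 48% to 55% of the time, depending on n, and that an 80% chance needs a true rate of about 82% to 83%. Adding subjects will not repair this while the hurdle equals the assumed rate.

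Under either route, say in 7.7 what follows if a cohort misses the criterion, and use one response definition and one time-point in both sections, consistent with the day 28 primary endpoint in 7.1.1. Settle this before day 28 results are reviewed. The cost is protocol wording only, with no extra subjects; the second route also means publishing a less favourable figure.

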**Anti-COVID19 Vaccination AKS-452X BOOSTER Study (Protocol nr. 901452-CT-21-001)**

---

minimum of 119 subjects for final analysis), that have an enhanced immune response as defined as following:

Enhanced immune response rate is defined as:

- i) Seroconversion based on a true positive based on the SP/RBD IgG ELISA assay positive/negative cutoff criteria using the quantitative cut-off value defined by the assay kit batch expressed in  $\mu\text{g/mL}$ . The positive/negative cutoff value was established as  $2.42 \mu\text{g/mL}$  from the validation analysis for the current lot of assay kits, but it should be noted that for each new lot of assay kits, Akston QC performs a re-validation of the cutoff value in order to maintain clinical agreement from lot-to-lot, and/or
- ii) Two times (2x) the baseline SP/RBD IgG at day 56 after a boosting, as compared to the titer at the time of screening (day 0).

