**Intervention:** One booster dose-level of naked AKS-452 (90 µg) administered via s.c. route in 150 subjects per cohort in which safety parameters and neutralizing IgG titers will be reviewed after the booster dose of 90 µg s.c.. Enhanced immune response is defined as: i) seroconversion based on a true positive based on the SP/RBD IgG ELISA assay positive/negative cutoff criteria using the quantitative cut-off value defined by the assay kit batch expressed in µg/mL. The positive/negative cutoff value was established as 2.42 µg/mL from the validation analysis for the current lot of assay kits, but it should be noted that for each new lot of assay kits, Akston QC performs a re-validation of the cutoff value in order to maintain clinical agreement from lot-to-lot, ii) two times (2x) the baseline SP/RBD IgG at day 56 after a boosting, as compared to the titer at the time of screening.

**Main study parameters/endpoints:** **Primary endpoint:** The percentage of patients that i) achieve an SP/RBD-specific IgG antibody titer level of  $\geq 2.42$  µg/mL at the day 28 time-point post-intervention (i.e. booster vaccine) if the base-line value prior to receiving the booster vaccine was  $< 2.42$  µg/mL or ii) where the SP/RBD-specific IgG antibody titer is at least 2x the base-line value prior to receiving the booster vaccine if the base-line value prior to receiving the booster vaccine was  $\geq 2.42$  µg/mL. The percentage of patients in each of the four cohorts that achieve the primary endpoint threshold at 28 days post-intervention will be calculated (n (%)). **Secondary endpoint:** Safety evaluation in the four cohorts for local and systemic adverse events after injection at each pre-defined scheduled follow-up (at 28, 56, 91, 182 and 273 days

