## 7. METHODS

### 7.1 Study parameters/endpoints

#### 7.1.1 Main study parameter/endpoint

**Main study parameters/endpoints: Primary endpoint:** The percentage of patients that i) achieve an SP/RBD-specific IgG antibody titer level of  $\geq 2.42 \mu\text{g/mL}$  at the day 28 time-point post-intervention (i.e. booster vaccine) if the base-line value prior to receiving the booster vaccine was  $< 2.42 \mu\text{g/mL}$  or ii) where the SP/RBD-specific IgG antibody titer is at least 2x the base-line value prior to receiving the booster vaccine if the base-line value prior to receiving the booster vaccine was  $\geq 2.42 \mu\text{g/mL}$ . The percentage of patients in each of the four cohorts that achieve the primary endpoint threshold at 28 days post-intervention will be calculated (n (%)).

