| Safety Assessments                                                     |                 |                      |                |          |          |           |            |
| Physical exam                                                                 | X               |                      |                |          |          |           |            |
| Vital signs                                                                   | X               | X                    |                |          |          |           |            |
| Blood pregnancy test c                                             | X               |                      |                |          |          |           |            |
| Urine pregnancy test c                                             |                 | X                    |                |          |          |           |            |
| Blood for safety a                                                 | X               | X                    |                |          |          |           |            |
| Vaccination Questionnaire                                                     |                 |                      | X f |          |          |           |            |
| Concomittant therapy, AEs/SAEs c                                   |                 | X                    | X              | X        | X        | X         | X          |
| Study Agent Administration/Pharmacokinetics and Immunology Assessments |                 |                      |                |          |          |           |            |
| Fc-conjugation vaccine administration d                            |                 | X                    |                |          |          |           |            |
| Peripheral blood for humoral responses                                        |                 | X g       | X              | X        | X        | X         | X          |
| Peripheral blood for PBMCs (cellular responses)                               |                 | X g       | X              |          |          | X         |            |

a) See Laboratory assessments for list of tests.

b) Using instant urine drug test kit

c) In all women

d) After vaccination, subjects are to be kept under medical supervision for 15 min.

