#### **7.5 Replacement of individual subjects after withdrawal**

Subjects who are withdrawn may be replaced until the intended number of subjects determined by the statistical assessment (i.e. a minimum of 119 subjects per cohort) is reached by this study. The SARS-CoV-2 IgG titer of day 28 can be used for the interim analysis of day 56.

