#### 9.6 Interim analysis (if applicable)

n.a.

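### The same immune response is judged at Day 28 against Day 0 in the primary endpoint and at Day 56 against screening in the mandatory 80% cohort criterion, and a Day-56 interim is both mentioned and ruled out

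*Protocol*

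**What the plan says.** **Day 28 against the pre-booster value.** Section 7.1.1 counts the subjects "that achieve the primary endpoint threshold at 28 days post-intervention will be calculated", with the value before the booster as baseline. The primary endpoint in the Summary is the same. Section 4.4, which defines the response rate used for the sample size, has "Two times (2x) the baseline SP/RBD IgG at day 28 after boosting, as compared to the titer just before vaccination (day 0". Section 9.3 states the primary aim at 4 weeks.

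**Day 56 against screening.** The Intervention paragraph of the Summary has "two times (2x) the baseline SP/RBD IgG at day 56 after a boosting, as compared to the titer at the time of screening". Section 7.7 makes it mandatory that a cohort of at least 119 subjects shows at least 80% response, and defines that response as "Two times (2x) the baseline SP/RBD IgG at day 56 after a boosting". The same clause names the reference titer: "at day 56 after a boosting, as compared to the titer at the time of screening (day 0". The bracketed day makes screening and Day 0 the same visit.

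**The schedule in 7.3.** Screening runs from Day -28 to Day -2 and is separate from Visit 1 on Day 0. The row "Peripheral blood for humoral responses" has its first entry on Day 0, with a footnote that the sample is taken before vaccination. Nothing is drawn for this purpose at screening.

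**The interim.** Section 7.5 says "The SARS-CoV-2 IgG titer of day 28 can be used for the interim analysis of day 56". Section 9.6, on interim analysis, answers that it does not apply.

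**The concern.** One response has two assessment days and two reference samples, and the two versions serve different purposes. Day 28 serves the primary endpoint and the sample size. Day 56 serves the only response criterion that the protocol calls mandatory for a cohort. Applied literally, 7.7 judges a cohort on a different day from its primary endpoint. If the choice is left until titers are known in an open-label study with no DSMB (8.5), it becomes a post hoc choice. The mention of an interim adds to this, because its status, content and consequences are undefined and another section denies that it exists.

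**Working it through.** **Step 1. Put the definitions side by side.**

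| Place | Assessment day | Reference titer |
|---|---|---|
| Summary, primary endpoint | 28 | before the booster |
| 4.4 | 28 | Day 0, just before vaccination |
| 7.1.1 | 28 | before the booster |
| 9.3 (aim) | 4 weeks | not stated |
| Summary, Intervention | 56 | screening, no day given |
| 7.7, mandatory 80% | 56 | screening, labelled Day 0 |

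The Summary contains both versions. Sections 4.4 and 7.7 use the same heading and almost the same wording, but differ in the day.

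**Step 2. Test Day 56 against the rest of the protocol.**
- The primary objective (2.1) covers 4-6 weeks, that is Day 28 to Day 42. Day 56 is 56/7 = 8 weeks.
- The mandatory criterion in 7.7 replaces subjects who drop out before Day 28. That suits a Day 28 assessment. Under 7.7 a subject lost between Day 28 and Day 56 is not replaced, yet has no Day 56 titer.
- No humoral sample is scheduled at screening. The Intervention paragraph's reference therefore has no scheduled sample, and the one in 7.7 is best read as Day 0 under the wrong label.

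**Step 3. Reproduce the plan's sample size.** Inputs from 4.4: null 0.70, alternative 0.80, one-sided alpha 0.05, power 0.80, null variance.

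n = [(1.645 × √(0.7 × 0.3) + 0.842 × √(0.8 × 0.2)) / 0.10]² = 118.9, so 119. This agrees with the plan. Allowing for 20% dropout, 119/0.8 = 148.75, so 149; the plan enrols 150.

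**Step 4. Compare the two hurdles at n = 119.**
- Planned test: 0.70 + 1.645 × √(0.21/119) = 0.769, and 0.769 × 119 = 91.5. It rejects from 92 responders (92/119 = 77.3%).
- Criterion in 7.7: 0.80 × 119 = 95.2, so 96 responders (96/119 = 80.7%).
- Exact probability of reaching each when the true rate is 0.70: 0.048 for 92 responders, 0.006 for 96.

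**Step 5. Sensitivity to the response rate on the chosen day.** The protocol gives no separate rates for Day 28 and Day 56, so the rates below are an assumed range.

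| True rate | Power of the planned test | Chance of at least 96/119 |
|---|---|---|
| 0.75 | 0.32 | 0.09 |
| 0.78 | 0.61 | 0.28 |
| 0.80 | 0.80 | 0.48 |
| 0.82 | 0.93 | 0.70 |
| 0.85 | 0.99 | 0.92 |

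**Step 6. How far the rate might move between days (illustration only).** Assume a log-normal fold-rise with SD(log10) of 0.3, 0.4 or 0.5, and 80% of subjects at 2x on Day 28. If titers are multiplied by d by Day 56, the rate becomes Φ(0.842 + log10(d)/SD).

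| d | SD 0.3 | SD 0.4 | SD 0.5 |
|---|---|---|---|
| 0.7 | 0.628 | 0.675 | 0.703 |
| 0.9 | 0.755 | 0.766 | 0.773 |
| 4/3.5 = 1.14 | 0.850 | 0.838 | 0.831 |

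The first two rows are assumed declines. The last takes the mouse data in 1.4, about 3.5-fold at two weeks and about 4-fold at Day 70, as if that ratio applied here. The SDs have no source in the protocol, and only the doubling limb is modelled; 7.7 joins it with and/or to the 2.42 µg/mL cutoff limb.

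**The case against.** The strongest reply is that Day 28 governs. Every formal statement of the primary endpoint says Day 28 against the pre-booster value, as does the definition beside the sample size; the Day 0 pre-dose sample is scheduled, and 119 reproduces. All of this stands, and it limits the point to the Intervention paragraph, 7.7 and 7.5. It does not remove the conflict, because 7.7 is current text and calls its criterion mandatory.

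The wording may have been carried over. The preceding study had a review after the Day 56 visit (section 3), and 7.3 here is still headed phase I. That may explain the error but does not correct it.

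Three stronger readings are tempting, and the documents support none of them:
- **Two chances at success.** The 80% criterion is an added requirement, not an alternative route. It needs 96 responders where the test needs 92, so requiring both lowers the chance of success. Section 7.7 also states no consequence for missing 80%, so calling it a go/no-go rule goes beyond the text.
- **Carrying Day 28 titers forward for withdrawn subjects.** Section 7.5 says only that the Day 28 titer may be used for the interim. Carry-forward is an inference from the section's subject. Nor does any section attach a boundary, alpha spending or a decision to that interim.
- **A lower response rate at Day 56.** No human kinetics after this booster are given, and the mouse titers did not fall. Starting from exactly 80%, any decline falls below 80% by construction. The illustration does not always cross the test boundary either: a 10% decline with SD 0.5 gives 0.7734, just above 92/119 = 0.7731.

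**Conclusion.** The point holds as an internal inconsistency that should be fixed. The protocol judges one response on two days against two differently named reference samples, and it both mentions and rules out an interim analysis. The Day 28 / Day 56 conflict has no reconciling reading. The conflict over the reference sample is smaller: 7.7 most naturally means the existing Day 0 sample, and only the Intervention paragraph names screening without a day.

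The consequence is that a cohort could meet the response criterion on one day and miss it on the other, in a direction the documents do not establish. The size depends on an unknown difference between the days. A five-point difference around 80% moves the chance of meeting the mandatory criterion from 0.48 to 0.09 or to 0.92. These figures rest on 119 evaluable subjects and assumed true rates. The formal primary endpoint and the sample size are not in error.

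**What to change.** - **Summary, Intervention paragraph, and 7.7:** state Day 28 against the pre-dose Day 0 sample as the single time point and baseline, in line with 4.4 and 7.1.1. Remove the references to screening as the baseline.
- **7.5:** delete the sentence on the Day-56 interim, so that the section agrees with 9.6.
- **Day 56 titers:** keep them as a secondary time point for kinetics.

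The cost is a wording amendment. The Day 0, 28 and 56 samples are already scheduled, and neither the sample size nor the visits change. The amendment should be made before any post-booster titers are reviewed.
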